### Procedure for unblinding if needed {17b}

This is an open-label trial, therefore unblinding is not necessary.

## Data collection and management

### Plans for assessment and collection of outcomes {18a}

All clinical study data will be registered in a REDCap database (electronic data collection form for clinical studies running on internal servers at Charité – Universitätsmedizin Berlin). The study timeline can be found in Fig. 1. To ensure that ED flow is not compromised through the study, parts of the baseline survey have been flexibilized.Baseline data:Sociodemographical data (e.g., age, sex, level of education)eHealth Literacy (eHEALS) [19]Self-reported health (MEHM) [20]Health anxiety (Item 1 of the German version of the Whiteley-Index WI-d, modified to Likert-scale) [21]Technical affinity (ATI-S) [22]Self-efficacy (ASKU) [23]Anxiety (VAS-A) [15]Patient’s stand-alone triage appraisalSymptom assessment data will be collected through the Ada Health appAn automatically in-app generated report will be downloaded and savedQuestionnaires pre-symptom assessment, after the symptom assessment (Ada), and after the physician encounter will be directly entered into the RedCap database by the participants. To reduce loss-to-follow-up, the survey after the physician encounter can be filled out up to 72h after the contact (e.g. on the ward or via telephone) if extraordinary circumstances prohibit the patient from taking the survey at the intended timepoint. Questionnaires used in the study are:PSQ [12]ZUF-8 [13]VAS-A [15]Trust scale of the CPQ [16]System Usability Scale (SUS) (only for the intervention group) [17]mHealth App Usability Questionnaire (MAUQ) (only for the intervention group) [18]Treating physicians fill out a paper-based survey after the first-patient encounter including the following items:Physician version of the PSQ [12]Triage appraisalRoutine clinical follow-up data after the patient-physician encounter will be collected by a study nurse and directly entered into the RedCap database.ICD-10 codesAssigned triage level (Manchester Triage System, MTS)Discharge typeLength of hospital stayDuration of waiting time

Patients not willing to participate in the trial will be offered to complete an anonymized version of the baseline survey in a paper-based form.

Data collection forms will be made available upon reasonable request by third, academic partners.

### Plans to promote participant retention and complete follow-up {18b}

The study period for each patient ends after discharge from the ED, not taking clinical record data into account. Therefore, no additional follow-up is necessary, where loss-to-follow-up may occur. Flexibility of assessments shall also improve retention. In addition, there are small financial incentives (vouchers) that will be handed out for completing all surveys up to t3 (Table 1).

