### Strategies to improve adherence to interventions {11c}

Patients will be informed about the study and the SAA and asked to participate. Since the intervention is implemented once only, no further measures for adherence improvement regarding the intervention are planned. Participants will receive small financial incentives (vouchers) if they complete the study, this also includes all study questionnaires.

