### Outcomes {12}

#### Primary outcome

The primary outcome is the participants’ satisfaction with the patient-physician-interaction as measured by the the Patient Satisfaction Questionnaire (PSQ) [12]. The intervention is considered successful if we find a mean difference in means of at least 5 points (Scale 0-100) in the intervention group compared to the control group after the first doctor’s contact before discharge, in exceptional cases by telephone within 72h.

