**Fig. 1 Fig1:**
[figure not shown]
Schematic illustration of a participant's journey through the 2-group parallel randomized controlled trial's phases of enrollment, allocation and data collection at multiple points in time during the visit

**Table 1 Tab1:** Schedule of events

Timepoint	Study period						
	Screening	Baseline	Treatment	Follow-up			
	***−t***_***1***_	0	***t***_***1***_ ***(after randomization)***	***t***_***2***_ ***(after symptom assessment)***	***t***_***3***_ ***(physician ecnounter)***	***t***_***4***_ ***(after physician encounter, up to 72h)***	***t***_***5***_ ***(post-discharge)***

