**Assessments**							
**Baseline variables**		X	X				
**Demographics**	X	X		X^a^		X^a^	
***Primary outcomes***						X	
***Secondary outcomes***				X		X	
***Routine clinical data***							X

^a^If ED flow prohibits patients from completing the survey at the intended timepoint

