### Sample size {14}

In the literature, a mean PSQ-5 score of 81 and a standard deviation of 14–17 can be found [13]. Assuming a clinically relevant difference of 5 points this amounts to a standardized mean difference of around 0.3.

For a fixed sample size design, the sample size required to achieve a power of 1-β = 0.80 for the two-sample *t*-test assuming equal variances at level *α* = 0.05 (two-sided) under these assumptions amounts to 2 × 176 = 352 patients needed (nQuery Advisor®, version 7.0). The drop-out rate is expected to be medium-sized (20%) due to organizational matters regarding patient flow in the ED. However, through guidance by the study personnel and small financial incentives attrition rates are tried to be kept down. Nevertheless, a potential dilution of the treatment effect due to drop-outs is considered. It is assumed that this can be compensated by additional 20 % of patients to be randomized, and therefore the total sample size required for a fixed sample size design amounts to *n* = 440 patients (220 patients per group).

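### Two sections set different conditions for the retention voucher, and one of them, read with Table 1, stops short of the only primary outcome survey

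*Protocol article*

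**What the plan says.** The voucher condition appears twice in the protocol article.

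- Plans to promote participant retention {18b}: "there are small financial incentives (vouchers) that will be handed out for completing all surveys up to t3 (Table 1".
- Strategies to improve adherence {11c}: "Participants will receive small financial incentives (vouchers) if they complete the study, this also includes all study questionnaires".

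The timepoints are fixed in Table 1. There t3 is the physician encounter and t4 is "after physician encounter, up to 72h". The row "Primary outcomes" has a single mark, at t4. The outcomes section agrees, placing the PSQ "after the first doctor’s contact before discharge, in exceptional cases by telephone within 72h".

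The sample size section {14} mentions the incentive after stating its drop-out assumption: "The drop-out rate is expected to be medium-sized (20%) due to organizational matters regarding patient flow in the ED". It then adds that "through guidance by the study personnel and small financial incentives attrition rates are tried to be kept down".

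**The concern.** Section {18b} cites Table 1, so its t3 has to be read with that table. On that reading the patient has met the condition by the time the physician is seen, and the survey that carries the primary outcome still lies ahead. Section {11c} says the reverse. Study nurses at three sites need one rule and are given two.

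The timing matters because the PSQ is analysed as a single final value (section {20a}). A patient who leaves without the t4 survey contributes no observed primary outcome. The same survey carries the ZUF-8 and the end-of-visit VAS-A. If t3 is meant literally, the voucher rewards every patient survey except this one.

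**Working it through.** **1. Table 1, by timepoint**

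| Timepoint | Definition | Assessments marked |
|---|---|---|
| 0 and t1 | baseline; after randomisation | baseline variables |
| t2 | after symptom assessment | secondary outcomes |
| t3 | physician encounter | none (only the intervention and usual-care rows) |
| t4 | after the encounter, up to 72 h | primary and secondary outcomes |
| t5 | post-discharge | routine clinical data |

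Demographics are also marked at screening and baseline, with a footnote allowing them at t2 or t4 if patient flow requires it. The t5 data are entered by a study nurse (section {18a}), so the last patient survey is at t4.

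**2. The two voucher rules set against the table**

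- Rule in {11c}: all questionnaires. Since t5 holds no patient survey, this means all surveys up to and including t4.
- Rule in {18b}: all surveys up to t3. Since t3 holds no assessment, this means nothing later than t2.

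**3. The rules by group**

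Section {6b} says that control patients fill in questionnaires only at the start of the wait and at the end of the visit. They therefore have no t2 survey.

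| Group | Needed under {11c} | Needed under {18b}, literally |
|---|---|---|
| Intervention | baseline, t2, t4 | baseline, t2 |
| Control | baseline, t4 | baseline only |

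The t4 survey drops out of the condition in both groups. What is left differs between them: two surveys in one group, one in the other.

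**4. Does the sample size depend on this?**

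Inputs from section {14}: "Assuming a clinically relevant difference of 5 points this amounts to a standardized mean difference of around 0.3"; two-sided α = 0.05; power 0.80; two-sample t-test; equal groups; drop-out 20%.

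- The t-test calculation (noncentral t) with d = 0.3 gives 175.4, rounded up to 176 per group, as stated.
- Evaluable total: 2 × 176 = 352, as stated.
- Randomised total: 352 / (1 − 0.20) = 440, or 220 per group, as stated.

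The voucher condition enters none of these steps, so aligning the two sections changes none of the figures.

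**5. Sensitivity only**

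The rates above 20% below are assumptions and are not in the protocol. With 220 randomised per group, n per group = 220 × (1 − drop-out), and d = 0.3:

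| Drop-out | n per group | Power |
|---|---|---|
| 20% (protocol) | 176 | 80.1% |
| 25% | 165 | 77.5% |
| 30% | 154 | 74.7% |
| 40% | 132 | 68.0% |

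The table shows that the design has no reserve beyond 20% loss. It does not estimate what the voucher wording does, because nothing in the protocol links the voucher to a drop-out rate.

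**The case against.** The strongest reply is that t3 is a labelling slip. Section {11c} states the full condition plainly. Table 1 marks no survey at t3, which makes t3 an odd place to end a survey requirement. Section {18a} describes three patient questionnaire occasions (before the symptom assessment, after it, and after the physician encounter), and t3 may stand for the third. Fig. 1 is not shown, so its labels cannot be checked. This reply is plausible, and it means that the protocol does not show the incentive to have been withdrawn from the t4 survey. It does not remove the conflict: {18b} points to Table 1 by name, and under that table the written rule is wrong.

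It is also fair to say that the voucher is not the only safeguard. Guidance by study personnel, flexible assessment times and late completion within 72 h all bear on the t4 survey.

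A reader might go further and infer two things that the text does not support.

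- *That the 20% drop-out assumption rests on the voucher.* Section {14} attributes the 20% to patient flow in the department. It names the incentive afterwards, beside staff guidance, as a means of holding attrition down, and derives no part of the 20% from it.
- *That {18b} denies any loss to follow-up.* It says that no follow-up beyond the emergency visit is needed. That sits a little loosely beside the 72 h exception, but it is not a claim that loss cannot occur and does not contradict the 20%.

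**Conclusion.** The point holds as an inconsistency between {11c} and {18b}, read with Table 1. It is more than a slip in background text, because it concerns an operating rule for the single survey that yields the primary outcome. If {18b} is followed literally, one of the two attrition measures named in the sample size section does not reach the PSQ, the ZUF-8 and the final VAS-A, and control patients earn the voucher for the baseline survey alone.

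That consequence is conditional on staff applying t3 as Table 1 defines it, which the protocol does not settle. The figures of 176, 352 and 440 stand. The effect on attrition, and so on power, cannot be quantified from the protocol. One might suppose that loss would follow satisfaction or group, but the protocol has no information on that either.

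**What to change.** In {18b}, change t3 to t4. This brings the section into line with {11c} and Table 1, since all surveys up to t4 are all the patient questionnaires there are. State that the rule is the same in both groups and that completion of the t4 survey on the ward or by telephone within 72 h also earns the voucher.

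Recruitment began in April 2022 and this version is dated 28 June 2022. The sponsor should therefore also establish which rule the sites have been using and, if it was the t3 rule, record the date of the change.

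The cost is a one-line correction and a note to the study nurses. Vouchers, sample size, assessments and analysis stay as planned. If the correction is handled as a protocol amendment, it takes the ethics committee route set out in section {25}.

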### Data management {19}

A data management and data protection plan was reviewed and approved by the clinical trial offices (an independent body) of the Charité – Universitätsmedizin Berlin. All data will be password protected on a server run by the Charité – Universitätsmedizin Berlin. Primary data, such as patient-reported outcomes, will be pseudonymized. Clinical data will be extracted from the electronic documentation system of the hospital into electronic case report forms (eCRFs). All extracted data is pseudonymized and will allow subsequent data linkage with patient-reported data from surveys. Range plausibility checks will be applied for data entry. Patients will answer questionnaires on tablets directly imported in RedCap.

### Confidentiality {27}

Only the principal investigator and authorized study members will be able to access the trial data at participating study sites. Recruitment logs will be kept at the local sites in locked cabinets. Pseudonymized data will be archived for 10 years.

### Plans for collection, laboratory evaluation, and storage of biological specimens for genetic or molecular analysis in this trial/future use {33}

Not applicable—see above (26b); there will be no biological specimens collected.

## Statistical methods

### Statistical methods for primary and secondary outcomes {20a}

R 4.0.2 or higher (R Core Team, 2022) and SAS 9.4 (SAS Institute, USA) will be used to perform statistical analyses. Baseline characteristics will be presented as percentages (binary data), median and interquartile range (ordinal data), and mean and standard deviation (continuous data). The primary efficacy endpoint is the mean difference in the patients’ rating of patient-physician interaction (PSQ-5) between the intervention group and the control group after patients have been treated (final value) and will be analyzed with a linear mixed model accounting for recruiting site. Secondary and exploratory efficacy endpoints will be analyzed using (generalized and mixed) linear models. Reporting will include the estimator, 95% confidence intervals, and respective *p* values. No adjustments of *p* values due to multiplicity are planned.

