### Trial design {8}

The study is a parallel-group, multi-center superiority trial with a randomization allocation ratio of 1:1 to either using a SAA before the physician encounter or physician encounter only (standard care) among non-urgent, self-referred walk-in patients in the ED.

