## Methods: participants, interventions, and outcomes

### Study setting {9}

The study is a local, multi-center ED-based study with three study sites located in Berlin, Germany. Two of the study sites are EDs of a large tertiary care hospital (Charité – Universitätsmedizin Berlin, Campus Mitte/Campus Virchow-Klinikum). One site is an emergency practice of the association of statutory health insurance physicians attached to the ED of a local hospital (Jüdisches Krankenhaus Berlin).

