### Eligibility criteria {10}

#### Inclusion criteria

Patients eligible for the trial must comply with all of the following at randomization:Age ≥ 18Treatment urgency assessed with the Manchester triage system: categorized as yellow (urgent, 30 min.), green (standard, 90 min.), or blue (non-urgent, 120 min.)Self-referred walk-inAdequate German or English language skillsThe patient is able to provide informed consent.

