## Assignment of interventions: allocation

### Sequence generation {16a}

The allocation sequence will be generated by the Institute of Medical Informatics, applying a permuted block design with random blocks stratified by study center using computer-generated random numbers. The block size will be concealed until the primary endpoint will be analyzed. Throughout the study, the randomization will be conducted by the Institute of Medical Informatics. The randomization list remains with the Institute of Medical Informatics for the whole duration of the study. Thus, randomization will be conducted without any influence of the principal investigator, study personnel, or physicians.

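### The primary model is valid but adjusts for site only; pre-specifying age, triage category and other pre-randomisation values would add modest precision, and the non-urgent label needs reconciling

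*Protocol article*

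**What the plan says.** **Model.** Under *Statistical methods for primary and secondary outcomes {20a}*, the primary endpoint is the mean PSQ-5 difference "between the intervention group and the control group after patients have been treated (final value"), and it "will be analyzed with a linear mixed model accounting for recruiting site". Site is the only adjustment named. The section does not say whether site is a fixed or a random term.

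**Sites and stratification.** *Study setting {9}*: "The study is a local, multi-center ED-based study with three study sites located in Berlin, Germany". *Sequence generation {16a}*: allocation is made by "applying a permuted block design with random blocks stratified by study center". The one factor in the model is therefore the one factor used in randomisation.

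**Baseline data.** *Plans for assessment and collection of outcomes {18a}* lists sociodemographic data, MEHM, VAS-A and other scales, but no baseline PSQ. *Methods for additional analyses {20b}* uses several of these, including age and MEHM, as subgroup criteria for the primary outcome. Triage category comes from the Manchester system. It is an eligibility criterion, and consent follows triage, so it is known before allocation.

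**Population.** *Trial design {8}* places the comparison "among non-urgent, self-referred walk-in patients in the ED", and the abstract likewise refers to a non-urgent triage category. *Inclusion criteria* admits patients "categorized as yellow (urgent, 30 min.), green (standard, 90 min.), or blue (non-urgent, 120 min".)

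**The concern.** Two things stand out.

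1. Satisfaction with a consultation may well vary with age, urgency, anxiety and general health. The trial holds these values, yet the stated primary model uses none of them. Whatever outcome variation they explain stays in the residual and widens the confidence interval. A mixed model with one outcome value per patient and site as the only named grouping also reads most naturally as a random site effect, and three sites are too few to estimate a variance well.

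2. The population label does not match the criterion. In the article's own terms, yellow is urgent and only blue is non-urgent. A result reported for non-urgent patients would describe a different group from the one enrolled.

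At stake are some precision on the primary endpoint and an accurate statement of whom the result applies to. Bias is not at stake.

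**Working it through.** **Step 1: reproduce the planned size.** Inputs from *Sample size {14}*: difference 5 points, standardised difference 0.3 (implied SD 5/0.3 = 16.67, within the quoted 14–17), two-sided alpha 0.05, power 0.80, drop-out 20%.

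- Normal approximation: n per group = 2(1.960 + 0.842)²/0.3² = 174.4, so 175.
- Two-sample t-test: 175.4, so 176 per group and 352 in total, as stated.
- Drop-out: 352/(1 − 0.20) = 440, as stated.
- Power with 176 per group at 0.3: 80.1%.

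The planned power takes no credit for covariates, so it does not depend on them.

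**Step 2: gain from covariates.** If baseline variables explain a share R² of PSQ variance, the residual SD is multiplied by √(1 − R²). The standardised difference becomes 0.3/√(1 − R²), and the 95% CI half-width is 1.96 × 16.67 × √(1 − R²) × √(2/176). The few degrees of freedom used by the covariates are ignored. R² is **assumed**.

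| R² (assumed) | Standardised difference | Power, 176 per group | CI half-width (points) | Analysed N for 80% power |
|---|---|---|---|---|
| 0 | 0.300 | 80.1% | 3.48 | 352 |
| 0.02 | 0.303 | 80.9% | 3.45 | 344 |
| 0.05 | 0.308 | 82.1% | 3.39 | 334 |
| 0.10 | 0.316 | 84.1% | 3.30 | 316 |
| 0.15 | 0.325 | 86.1% | 3.21 | 300 |

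**Step 3: site as a random effect, if that is what is meant.** Take three sites of about 117 patients, residual SD 16.67 and an assumed true site SD τ. The ANOVA estimate of the site variance is zero or negative when F(2, 349) falls below 1/(1 + 117τ²/16.67²).

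- τ = 0: threshold 1.00, probability 63%.
- τ = 1: threshold 1/1.421 = 0.704, probability 50%.
- τ = 2: threshold 1/2.684 = 0.373, probability 31%.

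At τ = 0, zero is the right answer. For the other cases, the consequence was simulated by dropping site altogether and comparing with fixed site effects (352 patients, balanced within site, difference 5, 4,000 runs).

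| Site SD | Power, site dropped | Power, site fixed |
|---|---|---|
| 0 | 79.2% | 79.2% |
| 1 | 80.7% | 80.8% |
| 2 | 80.2% | 80.4% |

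At site SD 2, the mean standard error was 1.782 without site and 1.774 with it. Site is then only about 4/16.67² = 1.4% of the variance. Type I error was 4.8–5.5% either way.

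**Step 4: validity of the site-only analysis when patients share physicians.** With 30 physicians nested in sites and an assumed physician intraclass correlation of 0.05 or 0.10, a site-only analysis with fixed site effects had type I error of 4.7% and 5.0% (1,500 runs each).

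**Step 5: which covariates are safely pre-randomisation.** Triage category and the age criterion are settled before allocation. VAS-A and MEHM are less certain. Table 1 places baseline variables both at time 0 and at t1, which it labels as after randomisation. The data collection section says parts of the baseline survey are flexible in timing, and demographics may be completed as late as t2 or t4.

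**Step 6: the label.** *Trial design {8}* and the abstract say non-urgent. *Inclusion criteria* names yellow as urgent (30 min), green as standard (90 min) and blue as non-urgent (120 min). *Recruitment {15}* counts MTS categories 3 to 5. The label fits one of the three enrolled categories.

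**The case against.** The strongest reply is that nothing in the model is wrong. Design and model agree on site, type I error holds, and the sample size reproduces without help from covariates. Every R² above is assumed, and without a baseline PSQ the true gain could lie at the low end, under one power point. A covariate list commonly sits in a full protocol or SAP, and neither is shown. Adjustment is not free either: with flexible baseline timing, requiring complete pre-randomisation values could drop patients from the intention-to-treat analysis.

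Most of this stands. It makes the point a recommendation for precision, and it means the fix must include a missing-covariate rule. It does not remove the point. The article states its primary model outright, and at least triage category and age can be used without collecting anything new.

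A reader might infer three stronger things that the document does not support:

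- *That three sites make the model fail.* The article does not say site is random. Even if the term dropped out, power changes by about 0.2 points or less in Step 3.
- *That ignoring the treating physician damages the primary analysis.* The article gives no number of physicians, caseload, intraclass correlation or physician code. It says only "Treating physicians fill out a paper-based survey after the first-patient encounter" and lists the items on the form. The physician is met after randomisation, so is not clearly a baseline covariate. For the physician PSQ, the planned class of generalised and mixed linear models already leaves room for a physician term. No gain can be quantified from the document.
- *That mixing urgency levels biases the result.* Randomisation protects the comparison. The label affects only whom the conclusion describes.

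**Conclusion.** The point holds as one of efficiency and clarity. The site-only primary analysis is valid and the planned power is as stated. Pre-specified baseline covariates would raise power from 80.1% to about 81–86% and narrow the CI half-width from 3.48 to between 3.45 and 3.21 points, if they explain 2–15% of PSQ variance. That range is an assumption. Stating site as fixed settles an ambiguity and avoids a poorly estimated variance, with negligible effect on the treatment estimate. It would be wrong to read this as an underpowered or biased trial.

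The conflict over non-urgent is a real inconsistency within the article and does not depend on any assumption.

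**What to change.** 1. **Primary model, section {20a}.** Specify final PSQ = treatment + site (fixed effect, 3 levels) + age + MTS category. Add baseline VAS-A and MEHM where recorded before randomisation. The treatment coefficient is still a mean difference in PSQ points, so the 5-point criterion reads as before.
2. **Missing covariates.** Add a simple rule, such as single mean imputation or a missing indicator, so that no patient leaves the intention-to-treat analysis for lack of a covariate. Treat a VAS-A or MEHM value recorded after randomisation as missing. Whether a value is available is then settled before allocation and cannot depend on arm.
3. **Population wording.** Reconcile the abstract and *Trial design {8}* with *Inclusion criteria*, so that conclusions name the triage categories actually enrolled.
4. **Physician.** Use a random physician intercept at most as a sensitivity analysis, mainly for the physician PSQ, and only if a physician code is available.

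Cost: a few lines of analysis text, slightly more analysis work and the missing-covariate rule, with no new data for items 1 to 3. Recruitment was already running when this version was dated, so the covariate set should be fixed before any outcome is analysed by arm.
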